#### Secondary radiological outcomes

##### DXA

Fifty-six patients will be included in this part of the study. DXA will be performed preoperatively to evaluate BMD of the proximal humerus and distal forearm. Bilateral BMD measurements of the proximal humerus and distal forearm will be used to adjust for changes in BMD that are not related to the shoulder arthroplasty. The primary value of interest is the difference in mean BMD between the preoperative score and 2-year follow-up. The precision of DXA will be evaluated by double examinations.

##### Plain radiographs

The radiographs are taken preoperatively, within the first week after surgery, at 3 months, and at 1 and 2 years. We use an anterior-posterior and a lateral view. The radiographs are used to evaluate the position of the component and to evaluate loosening as the cause of failure.

#### Secondary functional outcomes

##### Oxford shoulder score (OSS)

The OSS was conceived as a measurement tool for the assessment of pain and function after elective shoulder surgery [40]. There are 12 questions with each item scored from 0 to 4. The overall score ranges from 0 to 48, with 48 being the best. For ease of interpretation, the scores are converted to a percentage of the maximum score. The primary value of interest is the difference in mean score between the preoperative score and 2-year follow-up. We use a Danish version of OSS which was translated and validated with classical test theory [41]. The minimal clinically important difference for OSS has been suggested to be 6 points [42].

##### Constant-Murley score

The Constant-Murley score includes an assessment of pain, activities of daily living (ADL), range of motion, and strength. There are a possible 35 points given for the subjective assessment of pain and the ability to perform ADL. There are a possible 65 points given for an objective assessment, of which 40 points are allocated to range of motion and 25 points are allocated to strength. The maximum of 100 points indicates a shoulder with no disability. The primary value of interest is the difference in mean score between the preoperative score and 2-year follow-up. We use a Danish version [43] of the modified score described by Constant and colleagues in 2008 [44].

##### Pain and patient satisfaction

Pain on the day of examination is answered on a visual analogue scale (VAS) ranging from 0 to 100, with 100 being the worst. Patients are asked to categorize the result on a 7-point scale ranging from much worse to much better. The primary value of interest is the difference in mean score between the preoperative score and 2-year follow-up.

##### Side effects and complications

We will record any case of medical complications (embolism, cardiovascular event, pneumonia) and complications related to the surgical procedure (fractures, nerve injuries, deep and superficial infections, malpositioning of the components, instability, and dislocation) and revisions defined by removal or exchange of any component.

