The stemless humeral component is fixed only in the metaphysis (the wide portion of the long bones where bone growth occurs in childhood). By using this stemless metaphyseal fixation, the risk of a periprosthetic fracture and other stem-related complications can be reduced. There are also other advantages of the stemless design [11]. When using a stemmed humeral component, the inclination (the angle between the head and the shaft of the humerus) is given in advance. Even though the modern designs have variable inclination options to choose from, it can be difficult to restore the anatomy. With preoperative planning and precise cutting instrumentation of the stemless humeral component, the individual anatomy can, in theory, be more easily restored. In addition, the stemless design may be associated with shorter operation time compared with the stemmed design. Finally, because of the canal preserving design, the revision procedure is facilitated should the need of a revision arthroplasty arise, making the stemless design easier revisable. However, this is probably not as important as it used to be, since most modern stemmed designs have a common platform system which allows the stem to be retained in the case of revision to a reverse shoulder arthroplasty due to rotator cuff problems. The theoretical advantages of the stemless design may lead to a superior functional outcome compared with the stemmed total shoulder arthroplasty.

However, the stemless humeral component relies extensively on good metaphyseal bone quality, and the risk of osteolysis, stress shielding, and aseptic loosening may be higher than for the stemmed humeral component with peripheral fixation where the bone quality and density is superior to the central bone [12, 13]. This may lead to a higher risk of migration of the component.

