### Protocol violations, patient drop-out, and revision

If a stemless shoulder arthroplasty during the operation is regarded impossible to insert by the surgeon, the operation can be converted to either cemented or uncemented stemmed total shoulder arthroplasty or cemented or uncemented reversed shoulder arthroplasty. The uncemented stemmed shoulder arthroplasty can be converted to either cemented stemmed total shoulder arthroplasty or cemented reversed shoulder arthroplasty. The patient will be excluded according to the exclusion criteria, and the conversion will be recorded. If the conversion is performed after the randomization, then the patient will be excluded from the RSA and DXA analysis but included in the analysis of the functional outcome and the patient-reported outcome (intention-to-treat).

Patients who drop-out of the trial will be recorded, and the reason for drop-out will be noted. The patient will be included in the final mixed effects model analysis. Drop-outs before the 3-month evaluation cannot be included in the analysis. In addition, a sensitivity analysis will be carried out at the end of the study to assess the impact of missing data on the overall trial results. Patients who do not comply with rehabilitation will be recorded.

If a revision arthroplasty is needed, the reason and the new arthroplasty type are recorded. If possible, the patient is evaluated using RSA, DXA, clinical outcome, and patient-reported outcome prior to the revision procedure. The patient will remain in the study, and they are included in the 2-year analysis with their latest follow-up.

Major protocol modifications will be communicated to all investigators and trial registries immediately.

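### The complication list names fractures but not loosening or osteolysis, and outside the 56 RSA/DXA patients these have no stated outcome while the implant is unrevised

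*Protocol article*

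**What the plan says.** All references are to the protocol article.

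- **Background**, on the expected benefit: without a stem, "the risk of a periprosthetic fracture and other stem-related complications can be reduced".
- **Background**, on the expected price: with the stemless component, "the risk of osteolysis, stress shielding, and aseptic loosening may be higher than for the stemmed humeral component".
- **Side effects and complications**: besides medical events, the protocol records "complications related to the surgical procedure (fractures, nerve injuries, deep and superficial infections, malpositioning of the components, instability, and dislocation". Any operation in which a part of the implant is taken out or replaced counts as a revision and is recorded too.
- **Plain radiographs**: on timing, "The radiographs are taken preoperatively, within the first week after surgery, at 3 months, and at 1 and 2 years". On use, "The radiographs are used to evaluate the position of the component and to evaluate loosening as the cause of failure".
- **Protocol violations, patient drop-out, and revision**: "If a revision arthroplasty is needed, the reason and the new arthroplasty type are recorded".
- **Primary radiological outcome** and **DXA**: humeral migration by RSA and change in bone mineral density by DXA are measured in 56 patients.
- **Follow-up**: complications, revisions among them, are to be collected from hospital data and records at 10 years.

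**The concern.** Complications are a declared secondary outcome, and fewer stem-related complications are the reason for studying the stemless implant. A fair account of harm has to count the harms expected of each implant on similar terms. As written, a fracture is a complication whenever it occurs. Loosening or osteolysis enters the record only once it has led to failure or to removal or exchange of a component.

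A complication table built exactly to this list could omit events of the kind that the protocol itself expects to be commoner with the stemless component. A reader weighing the two implants on that table would have incomplete information. The 10-year collection would carry the same gap, at a point when the 2-year RSA and DXA measurements have long ended.

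**Working it through.** The article states no figure on this point, so there is none to reproduce. The check sets the sections side by side and then sizes the gap.

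**1. Match each named risk to a stated outcome**

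| Risk named in the Background | In the complication list? | Measured elsewhere? |
|---|---|---|
| Periprosthetic fracture (tied to the stem) | Yes, all patients | Not needed |
| Aseptic loosening (may be higher without a stem) | No | RSA migration in 56 patients; films, as a cause of failure; reason for revision |
| Osteolysis (may be higher without a stem) | No | Reason for revision; DXA is only indirectly related |
| Stress shielding (may be higher without a stem) | No | DXA bone density in 56 patients |

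The RSA and DXA outcomes are continuous measures compared between groups. They are not counts of patients with a loose or osteolytic component, and nothing says that they feed the complication record. RSA also covers the humeral component only.

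**2. Patients with neither RSA nor DXA**

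- Total 122 and RSA/DXA 56 (Randomization section): 122 − 56 = 66, and 66/122 = 54.1%.
- Stemless arm, with 1:1 allocation: 122/2 = 61. Planned RSA patients per group are 28, so 61 − 28 = 33 stemless patients have neither measurement.

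**3. Fractures that would be counted**

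The Background gives a periprosthetic humeral fracture prevalence of 1.6 to 2.4% after total shoulder arthroplasty. Applied to 61 stemmed patients:

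- 61 × 0.016 = 0.98
- 61 × 0.024 = 1.46

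About 1.0 to 1.5 fractures are expected.

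**4. Events that might go uncounted**

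The documents give no rate for radiographic loosening or osteolysis. Taking 3 to 10% by 2 years purely as an assumption, in the 33 stemless patients without RSA or DXA:

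- 33 × 0.03 = 0.99
- 33 × 0.10 = 3.3

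That is about 1.0 to 3.3 events, unless they led to failure or revision. This is a gross figure for one arm. The same events in the stemmed arm are equally unlisted, so the imbalance is the difference between the arms, which may be smaller.

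**5. Could fractures alone produce a significant difference?**

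With 61 per arm and no fracture in the stemless arm, Fisher's exact test (two-sided) gives p = 0.057 for 5 against 0 and p = 0.027 for 6 against 0. Six would be needed. The binomial chance of 6 or more among 61 is 0.04% at a rate of 1.6% and 0.34% at 2.4%. The concern is therefore how a small descriptive count reads, not a false significant result.

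**The case against.** The strongest reply is that the stemless risks are studied prominently. Humeral migration is a primary outcome with a stated hypothesis that the stemless component migrates more, bone density change is a secondary outcome, and revision is recorded with its reason. This stands, and it rules out any claim that the trial ignores these harms. It does not close the gap for the 66 patients without RSA or DXA, or for the complication count itself.

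A reader might go further and infer any of the following. The documents do not support them.

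- *The list is made of stem-type harms.* Only fracture is tied to the stem. Nerve injury, infection, malpositioning, instability and dislocation can occur in either arm, and one list serves both arms.
- *The safety comparison favours the stemless arm, or its direction would be reversed.* Multiplying 3 to 10% by all 61 stemless patients gives 1.8 to 6.1 events and seems to overturn the 1.0 to 1.5 fractures. But the rate is assumed, about 28 of those 61 have migration and bone density measured, and the sum takes it that no loosening occurs with a stem and no fracture without one. The Background says only that the risk may be higher. The Statistics section names no test for complications.
- *Loosening in an unfailed implant is certain to be disregarded.* The films are scheduled for everyone, and the wording on failure may simply be loose. What can be said is that no outcome is stated for it.
- *Rotator cuff failure is part of the same imbalance.* The Background mentions "revision to a reverse shoulder arthroplasty due to rotator cuff problems", but as a reason for revision and not as a stemless risk, and reasons for revision are recorded.

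Finally, this is a condensed article, and the full protocol may define complications and film reading in more detail. That is a fair caution. Still, the article does set out a list, and the list does not match its own statement of risk.

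**Conclusion.** The point holds as a gap in how harm is defined. The complication list includes the harm tied to the stem and omits those that the Background says may be more frequent without one. In 66 of 122 patients (54%), about 33 of them stemless, loosening or osteolysis short of revision has no stated outcome, and the 10-year collection inherits the list.

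The complication count can therefore be incomplete in a direction that may favour the stemless arm. How far is unknown. The illustration of 1.0 to 3.3 missed events against 1.0 to 1.5 fractures rests on an assumed rate of 3 to 10%, on 28 stemless patients in the RSA/DXA part, and on the quoted fracture prevalence applying to the stemmed arm. At its low end the two figures are about equal. With counts this small, one or two events could change how the table reads, but bias has not been shown. The two primary outcomes are not affected. The change is worth making because it is cheap and concerns a declared secondary outcome.

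**What to change.** - **Side effects and complications**: add component loosening, and osteolysis or progressive radiolucency, to the surgical complications recorded.
- **Plain radiographs**: state that the films already scheduled at 3 months, 1 year and 2 years are read for these signs in all 122 patients, whether or not the implant has failed, and in the same way in both arms.
- **Reporting**: give the counts by randomised arm, with fractures and the added events side by side.
- **Follow-up**: use the same list for the 10-year collection.

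A separate grade for stress shielding and an entry for rotator cuff failure are optional, and the point does not depend on them.

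The cost is a few extra fields on the complication and film-reading forms, and the time to complete them. No additional imaging is needed. Reported complication rates will be somewhat higher, which should be explained when they are compared with series that did not count these events.

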##### Economic evaluation

In modern health economics, thresholds have been estimated for acceptable cost-utility ratios—the threshold for how much health care providers will pay for an extra quality-adjusted life year (QALY). In England and in Europe, the threshold for an extra QALY is set at 20,000–30,000 pounds and 30,000 Euros, respectively. The cost utility of the Comprehensive Nano stemless shoulder arthroplasty will be compared with these thresholds and with the cost utility of the uncemented Comprehensive stemmed total shoulder arthroplasty. The EQ-5D-5L will be used to estimate QALY for individual patients. The primary value of interest is the difference in mean score between the preoperative score and 2-year follow-up. A cost model will be defined using data from patients, clinical records, registries, and unit costs from the Danish health care system. We will record length of hospital stay, discharge destination, pain medication usage, and readmission.

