### Follow-up

All patients will be followed actively for 2 years (Figs. 2 and 3) with evaluation at 3, 6, 12, and 24 months from the day of surgery (and randomization). Data on complications including revision will be extracted from the hospital database and patient records after 10 years.

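### The economic plan sets the stemless implant's own cost utility against a threshold for an extra QALY, where the stemless-versus-stemmed incremental ratio is needed

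*Protocol article*

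**What the plan says.** Everything at issue stands in the Economic evaluation section of the protocol article.

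- Thresholds: for England and Europe, "the threshold for an extra QALY is set at 20,000–30,000 pounds and 30,000 Euros, respectively". The unit is an additional QALY.
- Comparison: "The cost utility of the Comprehensive Nano stemless shoulder arthroplasty will be compared with these thresholds and with the cost utility of the uncemented" stemmed implant. The section names no ratio of extra cost to extra QALYs.
- QALYs: "The EQ-5D-5L will be used to estimate QALY for individual patients". How utilities become QALYs is not described.
- Summary value, in the next sentence: "The primary value of interest is the difference in mean score between the preoperative score and 2-year follow-up". The same sentence serves the WOOS, the Oxford score, the Constant-Murley score and pain.
- Costs: "A cost model will be defined using data from patients, clinical records, registries, and unit costs from the Danish health care system". No expected cost, utility or QALY difference is given.

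The Follow-up section places visits at 3, 6, 12 and 24 months. The Enrolment section lists EQ-5D-5L among the preoperative questionnaires.

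**The concern.** A threshold for an extra QALY answers one question: is what the new option adds over the alternative worth what it adds in cost? Here the alternative is the stemmed implant. The section instead sets the stemless implant's own ratio against the threshold. That ratio mostly reflects the benefit of having a shoulder replacement at all, which both arms receive. The Background calls total shoulder replacement effective for this condition, and the Discussion says the two components are currently considered equal. A small QALY difference on top of a large shared gain is therefore plausible, and in that situation the own ratio says least about the choice between implants.

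A second, lesser matter is the value of interest. A QALY is utility accumulated over time. A two-point change cannot register a faster recovery, or an early setback, that has evened out by 2 years. If it were used as the QALY measure, such differences would be lost.

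At stake is a published statement that the stemless implant is, or is not, cost-effective, when the between-arm data could point the other way.

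**Working it through.** The section states no ratio or expected difference, so there is no figure of the plan to reproduce. **All costs and utilities below are assumptions**; only the EUR 30,000 threshold and the visit times come from the article.

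**1. Which ratio is described.** An incremental ratio of stemless over stemmed is a single number with no stemmed counterpart. The section compares a stemless cost utility with a stemmed one, so each must belong to one implant.

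**2. Formulas.** With cost C and QALYs gained Q:
- own ratio = C / Q
- incremental ratio = (C_stemless − C_stemmed) / (Q_stemless − Q_stemmed)

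If stemless gains more QALYs, its own ratio is a weighted average of the stemmed own ratio and the incremental ratio, with weight Q_stemmed / Q_stemless on the former. At 0.40 and 0.41 QALY that weight is 0.40 / 0.41 = 0.976, so the incremental ratio hardly shows.

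**3. Simple case.** Stemless EUR 8,000 for 0.40 QALY; stemmed EUR 7,000 for 0.39.
- Own ratios: 8,000 / 0.40 = 20,000; 7,000 / 0.39 = 17,949.
- Incremental: 1,000 / 0.01 = 100,000.

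The stemless own ratio passes 30,000; the incremental ratio does not.

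**4. Range.** Stemmed fixed at EUR 10,000 and 0.40 QALY gained (own ratio 25,000). Cells show the stemless own ratio, then the incremental ratio.

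| Extra cost (EUR) | +0.01 QALY | +0.02 | +0.05 | +0.10 |
|---|---|---|---|---|
| 500 | 25,610 / 50,000 | 25,000 / 25,000 | 23,333 / 10,000 | 21,000 / 5,000 |
| 1,000 | 26,829 / 100,000 | 26,190 / 50,000 | 24,444 / 20,000 | 22,000 / 10,000 |
| 2,000 | 29,268 / 200,000 | 28,571 / 100,000 | 26,667 / 40,000 | 24,000 / 20,000 |

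The own ratio passes 30,000 in all 12 cells. The incremental ratio exceeds it in 6.

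**5. The other direction.** Stemmed EUR 13,900 for 0.40; stemless EUR 14,000 for 0.41.
- Own ratios: 34,750 and 34,146, so stemless fails.
- Incremental: 100 / 0.01 = 10,000, which passes.

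**6. Two-point change against area under the curve.** Assumed utilities at 0, 3, 6, 12 and 24 months: stemmed 0.55, 0.65, 0.72, 0.80, 0.80; stemless 0.55, 0.75, 0.80, 0.80, 0.80. Trapezoid areas in years:
- stemmed: 0.15 + 0.17125 + 0.38 + 0.80 = 1.50125
- stemless: 0.1625 + 0.19375 + 0.40 + 0.80 = 1.55625

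The difference is 0.055 QALY. The change from baseline to 2 years is 0.25 in both arms, a difference of 0. Subtracting 2 × 0.55 = 1.10 gives gains of 0.40125 and 0.45625. At costs of EUR 10,000 (stemmed) and 12,000 (stemless):
- own ratios per QALY gained: 24,922 and 26,301
- incremental: 2,000 / 0.055 = 36,364

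The article does not give the denominator. With total QALYs instead of gains, the stemless own ratio is 12,000 / 1.55625 = 7,711, further under the threshold, and the incremental ratio is unchanged.

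**The case against.** The strongest reply is that this is loose wording in a condensed article. The section calls the threshold incremental, names the stemmed arm as comparator and defers the cost model, so a full economic plan may well contain the right ratio. Formula, integration rule and interval are details an article may leave out. That is fair as to omissions, and none of them is held against the plan. What remains is a comparison the article does state, and as stated it puts the wrong quantity against the threshold.

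Four stronger readings are tempting and are not supported:

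- *Both implants are tested against the threshold.* Only the stemless one is; the stemmed ratio serves as its comparator.
- *The randomised comparison goes unused.* The stemmed control arm is in the quoted sentence. In all six cells above where the incremental ratio exceeds 30,000, the stemless own ratio is also higher than the stemmed 25,000, so the head-to-head comparison would give some warning. It would not give the price per extra QALY that the threshold is meant to judge.
- *QALYs will be computed from two time points.* The change score stands next to individual QALYs, in a sentence repeated across outcomes, and does not expressly replace them. The loss in step 6 arises only if it is used that way.
- *EQ-5D-5L is collected at every visit.* The visits exist, but the Follow-up text does not list instruments and the schedules in Figs. 2 and 3 could not be read for this check.

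It is also true that the illustrations show only that a reversal is possible. In 6 of the 12 cells the conclusion at EUR 30,000 is the same either way.

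**Conclusion.** The point holds for the threshold comparison. The article defines a threshold for an extra QALY and plans to judge the stemless implant's own cost utility by it, with no incremental ratio stated. Under assumed inputs this can reverse the conclusion in either direction: 20,000 against 100,000 in one example, 34,146 against 10,000 in another. How likely a reversal is in this trial cannot be said, because the article gives no costs or utilities. The risk is greatest if the QALY difference between implants is small relative to the shared gain.

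On the value of interest the conclusion is conditional. If the change to 2 years were used as the QALY measure, a utility gap of 0.05 lasting 6 to 12 months and gone by 2 years would count as zero instead of 0.05 × 0.5 = 0.025 to 0.05 × 1 = 0.05 QALY. At EUR 30,000 per QALY that is EUR 750 to 1,500.

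This is a secondary outcome. The two primary endpoints and the sample size are untouched. It should be corrected before the economic analysis is run.

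**What to change.** Reword the Economic evaluation section, or settle the following in the analysis plan:

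1. Apply the thresholds to the between-arm result: incremental cost per QALY of stemless over stemmed, or incremental net benefit at the stated thresholds, with an interval (a bootstrap would do). Net benefit behaves better if the QALY difference is close to zero.
2. Drop the comparison of the stemless arm's own ratio with the threshold.
3. State that QALYs are the area under each patient's EQ-5D-5L utility curve over the visits at which it is collected, with the between-arm difference adjusted for baseline utility. Confirm whether EQ-5D-5L is collected at each of the 3, 6, 12 and 24-month visits.
4. Keep the change from before surgery to 2 years only as a descriptive EQ-5D score outcome.

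The cost is rewording and modest extra analysis work. No new visits are needed. The trial was sized for migration and WOOS, so the interval around the incremental result may be wide and should be reported as such.
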